#### Qualitative analyses

Qualitative data will be longitudinally embedded into data collection during implementation to describe components of the implementation process and outcomes that cannot be answered quantitatively [104, 105]. We will use thematic analysis [106–108] and an abductive approach wherein we first generate codes inductively (e.g., emergent from the data) and then deductively (e.g., informed by the implementation frameworks). Inductive analysis will allow for unbiased description of the implementation process from center directors and supervisors and the creation of inductive codes. The deductive analysis will include integrating codes informed by CFIR and RE-AIM to capture the *why* and *how* of successful (or unsuccessful) implementation processes and outcomes (e.g., providers’ day-to-day perception of how supervision facilitated implementation, on-the-ground barriers to implementation not captured by the surveys). Sample sizes for the qualitative interviews will be sufficient to meet saturation (e.g., hearing it all and understanding it all for each implementation domain [109, 110]. All qualitative analyses will be conducted using Nvivo [111].

### Ethical considerations

This study has been approved by the Yale University Human Subjects Committee (2000035211) and has been registered at ClinicalTrials.gov (NCT05890404). The trial poses no greater than minimal risk to participants. The study team has taken every possible step to minimize breach of confidentiality. All research team members undergo privacy and confidentiality training, and participants will be assigned unique study identification numbers, keeping their survey and interview data separate from identifiable information. The consent documentation clearly delineates these risks and protections to participants. All participants (i.e., directors, providers, local supervisors, and clients) will provide consent electronically before completing their first survey.

A data and safety monitoring board (DSMB) will be convened annually to review study conduct, discuss potential safety and logistical concerns, and make recommendations regarding the resolution of these concerns and the status of the trial. This DSMB will be composed of experts in the field, and its members will not be affiliated with the study sponsor. Adverse events will be evaluated by PI [name] on a real-time basis and classified as serious (mild, moderate, severe) or non-serious, and appropriate reporting procedures will be followed for this. Important protocol modifications related to the safety of participants will be shared promptly with the National Institutes of Health and the Yale University Human Subjects Committee throughout the study. There are no plans to conduct independent audits or interim analyses of primary outcomes regarding the termination of the trial. 

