### Randomization

Upon receiving 90 signed memoranda of understanding, the 90 LGBTQ community centers will be randomized in a 1:1:1 ratio to receive one of the three implementation strategies. Randomization will be stratified by director report of anticipated staff participation. Specifically, high-attendance centers will be operationalized as those with greater than the median number of anticipated providers across the 90 enrolled centers whereas low-attendance centers will be operationalized as those that anticipate fewer than the median number of providers per center. Centers whose anticipated number of providers is at the median will be randomly and evenly divided across the two groups. The 15 effectiveness centers will be randomized separately to ensure their equal distribution across the three implementation strategies. Randomization allocation will be generated by the study statistician and assigned by the study coordinator. All participants and study staff will be unmasked to condition assignment, as necessitated by the study design.

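### The adverse-event rule makes intensity a sub-level of seriousness and, as stated, gives non-serious events no severity grade

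*Protocol article*

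**What the plan says.** The only rule for adverse events in the protocol article is in Ethical considerations. The evaluator is named ("Adverse events will be evaluated by PI") and is to work in real time. Events are then to be "classified as serious (mild, moderate, severe) or non-serious, and appropriate reporting procedures will be followed for this". The same section sets up a monitoring board ("A data and safety monitoring board (DSMB) will be convened annually to review study conduct, discuss potential safety and logistical concerns") and rates the risk of the study: "The trial poses no greater than minimal risk to participants".

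The article defines neither seriousness nor severity, and no other section grades adverse events.

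**The concern.** Seriousness and severity answer different questions. Seriousness is about the outcome of an event and normally decides how and how fast it is reported. Severity is about intensity. Neither determines the other: an intense episode of distress may meet no seriousness criterion, and an event that does meet one may be of moderate intensity.

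The sentence in Ethical considerations treats one attribute as a subdivision of the other. Taken at its word, an event has to be serious before its intensity is recorded. A marked but non-serious worsening and a trivial complaint would then carry the same label.

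This is relevant here because the trial enrolls mental health clients. The sections Clients and Effectiveness outcome analysis, with its sample size justification, describe people receiving mental or behavioral health services at 15 centers, with 780 expected. Worsening symptoms or distress are a plausible kind of adverse event in such a group, and their intensity is part of what a safety record should hold. If the event form follows the sentence literally, the intensity of non-serious events may be hard to recover afterwards.

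**Working it through.** There is no stated figure to reproduce. The check is a reading of the rule and a count of the classes it creates.

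**Step 1: the stated rule.** The parenthesis with the three grades follows the word serious, and the word non-serious stands alone. The classes are:

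- serious, mild
- serious, moderate
- serious, severe
- non-serious (no grade)

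Count: 3 + 1 = 4.

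**Step 2: two separate classifications.** Seriousness has 2 levels and severity has 3. Count: 2 × 3 = 6.

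**Step 3: where the difference lies.** All three serious cells survive under the stated rule. The three non-serious cells (mild, moderate, severe) become one. The difference, 6 − 4 = 2, comes entirely from the non-serious side. This counts labels only. It says nothing about how many events would be affected, because the article gives no adverse-event rates.

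**Step 4: does anything else supply the missing grade?** The rest of the article has no definition of seriousness, no severity scale and no grading of non-serious events. Table 1 lists client symptom scales, but as effectiveness outcomes at scheduled surveys and not as adverse-event records.

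**Step 5: what the rule leaves intact.** Every event is still sorted into serious or non-serious. If reporting follows seriousness, the information needed to trigger it is present even on the literal reading. What the stated rule lacks is the intensity of non-serious events.

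**The case against.** The strongest reply is that this is one compressed sentence in a journal article. Seriousness criteria, grading scales, event forms and reporting routes are usually set out in a full protocol or a data and safety monitoring plan, which is not shown here. The parenthesis may simply be misplaced, and the form in use may already record both attributes. The trial is described as minimal risk, and clients are study participants at only 15 of the 90 centers. Their depression, suicidality, anxiety and substance use are measured on standardized scales at baseline and 4, 8, 12 and 24 months, with depression (PHQ-9), anxiety and substance use compared by strategy, so worsening is captured in another way.

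Much of this stands, and it limits the point. It does not remove it. Had the article said only that events will be classified and reported, there would be nothing to raise. It states a classification instead, and that classification is faulty. Scheduled symptom scores are also not a grade on an adverse-event record.

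A reader might infer more, and the document does not support it:

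- **That the monitoring board's reports are confused, or that the board cannot see graded harm by strategy.** The article describes an annual review of possible safety concerns and does not say what adverse-event material the board receives. Nor does it say whether the board sees the symptom data during the trial.
- **That non-serious events will never be graded.** The text shows only that the stated rule provides no grade. Practice may differ.
- **That reporting itself will go wrong.** The serious/non-serious split is kept, and no route from the misplaced grades to a missed report is shown.
- **That most harms in this trial would be severe but non-serious.** No adverse-event rates or expected types are given.
- **That the open design makes this worse.** Randomization states that "All participants and study staff will be unmasked to condition assignment", but this is disclosed as a necessity of the design and has no bearing on whether intensity is nested in seriousness.

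**Conclusion.** The point holds as a modest correction to a stated safety rule. As written, the rule makes intensity a sub-level of seriousness and gives non-serious events no severity grade: four classes instead of six, with the whole loss among non-serious events.

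This rests on two assumptions: that the sentence is read as it stands, and that seriousness and severity carry their usual separate meanings, since the article defines neither. If the operational form already records both, only the wording is wrong. If it follows the sentence, the intensity of non-serious events will not be on record.

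No efficacy comparison, error rate, power statement or sample-size figure is touched.

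**What to change.** Rewrite the sentence in Ethical considerations so that every adverse event receives two separate classifications:

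1. serious, yes or no, which determines the reporting procedure;
2. severity, as mild, moderate or severe, whether or not the event is serious.

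Then check that the event form carries both items for every event. The cost is one sentence and at most one extra form field. If the form already has both, only the text changes. No new procedure for the monitoring board is needed to correct this; having it confirm the investigator's classifications would go beyond the defect.

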### Dissemination

The final trial dataset will be available to all study investigators. Deidentified data for participants who have agreed to have their data shared will be submitted to the National Institutes of Mental Health Data Archive. In addition, the data and statistical code will be available by request to qualified researchers. To ensure that results of this research increase the likelihood that SGM individuals nationwide receive LGBTQ-affirmative CBT — one of the only EBPs developed to address SGM individuals’ mental health — and therefore have the strongest possible effect on SGM mental health disparities, we have planned for six months of dissemination activities. We will first present results to a community advisory board (CAB) of 12 directors, providers, and SGM community members to gain interpretive feedback and suggestions for dissemination activities. We will then summarize study results in an accessible research brief and accompanying webinar for all LGBTQ community center directors nationwide.

The brief and webinar content, which the CAB will review and shape, will identify the most effective implementation strategies for a variety of center-level conditions and specify barriers and facilitators of successful implementation so that center directors and providers can select implementation strategies accordingly. Alongside these results, we will instruct centers on how to access all implementation materials (i.e., for providers, supervisors, and clients) through our training platform. This dissemination phase will also allow us to explore centers’ maintenance or discontinuation of implementation strategies through exploratory interviews with directors and providers at centers representing diverse geographies, budgets, and staff and client makeup. These activities will inform future planning and needed supports on the part of community organizations, funders, and academic researchers to ensure that SGM continue to benefit from this and any future EBP capable of reaching SGM individuals across high-need, low-resource settings.

Authorship for manuscripts will be determined using the four criteria established by The International Committee of Medical Journal Editors [112]. Significant contribution for authorship includes contributions to the study conceptualization, study design, or data collection, analysis, or interpretation; drafting or critically reviewing the manuscript; approval of the final version of the manuscript; and the agreement to be held responsible for all aspects of the study and to assist in investigating any concerns about the study’s accuracy or integrity. An individual must meet each of these criteria to be considered as an author.

## Discussion

Although sexual and gender minority populations experience among the largest mental health disparities of any population, evidence-based mental health practice specifically targeting their distinct stressors and stress responses has been unavailable until recently. Now that LGBTQ-affirmative CBT has demonstrated efficacy across several trials and generated high demand, implementation science is needed to determine optimal nationwide implementation strategies. This type III hybrid effectiveness-implementation trial will identify the optimal means through which to implement this treatment in the US’s large network of LGBTQ community centers, thereby producing generalizable guidance for evidence-based practice (EBP) implementation across low-resource settings nationwide in which mental health disparity populations are likely to seek treatment.

This study represents the first to take advantage of the nationwide network of LGBTQ community centers, an innovative site for EBP implementation, to study the implementation of mental health EBP. National mental health networks are rare, yet the LGBTQ community created its own network of affirmative care settings to meet the needs of its members [53]. Coordinated by our partner CenterLink, this network of low-resource, frontline settings presents an innovative opportunity to broadly test the delivery of LGBTQ-affirmative CBT in these community settings. The study’s methods directly embrace features of low-resource mental healthcare settings (e.g., high volunteer staff, high turnover) to inform optimal implementation in such settings. First, by comparing three additive training levels, this study can determine the minimum training necessary in resource-constrained contexts. Second, recognizing that LGBTQ centers often rely on volunteers and trainees with high turnover, this study will follow providers over 24 months and assess relocation features for those who have moved (e.g., type of setting and continued fidelity to LGBTQ-affirmative CBT [113]). Third, this study will assess whether center leaders support LGBTQ-affirmative CBT as a way to overcome resource constraints (e.g., because it is time-limited and can attract funding). Finally, the local SGM policy context is constantly shifting, with impact on SGM clients’ mental health and centers’ ability to address it. The study team possesses expertise in studying policy impact on SGM mental health [8, 114, 115] and will assess the SGM policy context of each center as a moderator of implementation success [116]. This study advances implementation science using a rare opportunity to study EBP implementation in frontline settings in a key mental health disparity population.

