We hypothesize that these three additive training implementation strategies will predict respective graduated increases in implementation success at 4-, 8-, 12-, and 24-months post-training (see Figs. 1 and [67]). That is, we predict that reach, effectiveness, adoption, implementation, and maintenance will be higher in the Local Supervision condition relative to the Direct Training condition and that the Direct Training condition’s implementation outcomes will be higher than the Materials Only condition. Drawing on theories of organizational [68, 69] and provider [70–73] change, we also hypothesize that organizational (e.g., shared norms of the importance of EBP) and provider (e.g., self-efficacy for EBP delivery) factors will mediate the stronger impact of the more intensive training strategies on implementation success and client mental health outcomes. To facilitate this latter aim, in a subset of 15 LGBTQ community centers (five centers per condition), we will compare the three training implementation strategies in terms of client mental health symptom change from before implementation to 4, 8, 12, and 24 months after.

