#### Provider implementation fidelity outcome analyses

We will summarize provider characteristics (e.g., volunteer status, length of SGM service) overall and by implementation strategy and assess for baseline imbalances. We will then compare the implementation outcomes for the Materials Only condition vs. Direct Training vs. Local Supervision. The primary implementation outcome is provider implementation fidelity (assessed via simulated practice responses) at 8-month follow-up; secondary outcomes include 8-month provider self-efficacy, competency, familiarity, and use of LGBTQ-affirmative CBT. For primary and secondary outcomes, will use mixed effects models [93] with the identity link function to compare the effect of implementation strategies. The fixed effects include the time effect and the time × implementation strategies interaction terms; the random effects include center and within-provider repeated measures. We will use the robust score test to assess whether the interaction terms are significantly different across the three strategies, with a 0.05 overall Type I error rate, and a 0.025 error rate for each of the two primary strategy comparisons. For secondary outcomes, we will compare implementation strategies with a 0.05 Type I error rate. We will re-run these analyses with 12- and 24-month outcomes to determine implementation maintenance.

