##### Sample size justification

Provider implementation fidelity serves as our primary outcome used to estimate sample size given its role in linking provider behavior to client mental health [84, 94–96]. We estimate that approximately six mental health providers will enroll per center, or about 540 providers total. Power was computed to test the null hypotheses of no difference between Materials Only and Direct Training and between Direct Training and Local Supervision in a cluster trial. For the primary implementation outcome, the change from baseline to 8-month follow-up was estimated as 0.14 for the Direct Training strategy and its variance was estimated as 0.0439 using data obtained from the waitlist-controlled trial [57]. Thus, the standardized change for the Direct Training strategy was estimated at 0.67. With a 0.025 Type I error rate, allowing for two primary comparisons between the three strategies, we will have 80% power to detect an effect of *d* = 0.34–0.46 on the 8-month change of the primary outcome, assuming a between-center ICC ≤ 0.1. In other words, we will have 80% power to detect the difference between Materials Only and Direct Training when the standardized change for Materials Only is ≤ 0.21–0.33, and we will have 80% power to detect the difference between Direct Training and Local Supervision when the standardized change for the Local Supervision strategy is ≥ 1.01–1.13.

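### The Discussion says the trial can determine the minimum training necessary, but the planned tests can show only that an added level helps, not that a lower level is enough

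*Protocol article*

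**What the plan says.** The Discussion lists ways in which the design suits low-resource settings. The first is that "by comparing three additive training levels, this study can determine the minimum training necessary in resource-constrained contexts".

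The rest of the article sets up a superiority trial:

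- **Hypothesis (Background):** "these three additive training implementation strategies will predict respective graduated increases in implementation success", with Local Supervision above Direct Training and Direct Training above Materials Only.
- **Primary analysis (Provider implementation fidelity outcome analyses):** a robust score test for any difference among the three arms in their time-by-strategy terms. Its error rates are set out in these words: "with a 0.05 overall Type I error rate, and a 0.025 error rate for each of the two primary strategy comparisons".
- **Power (Sample size justification for fidelity):** "Power was computed to test the null hypotheses of no difference between Materials Only and Direct Training and between Direct Training and Local Supervision".
- **Client outcome (Effectiveness outcome analysis and its sample size justification):** the same adjacent pairs, again with null hypotheses of no difference, for the PHQ-9.

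The article states no non-inferiority or equivalence margin, no smallest important difference, no threshold for adequate fidelity, and no rule for concluding that a lower level is enough. The Dissemination section commits to a research brief and webinar for center directors nationwide, to help them choose among the strategies.

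**The concern.** To call a level the minimum necessary is a claim of sufficiency: the next level up adds nothing large enough to matter. A test of no difference supports a claim in one direction only. If it rejects, the higher level adds something. If it does not reject, the data may fit no benefit, a small benefit or a worthwhile one, and the test does not separate these.

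Without a margin or an adequacy threshold, a non-significant step is the only thing in the stated plan from which sufficiency could be drawn. The results go to directors of centers with small budgets, for whom the cheaper option is attractive. A non-significant Local Supervision versus Direct Training comparison, read through the Discussion sentence, could become advice that supervision is not needed while the interval still includes a substantial gain.

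**Working it through.** **Inputs from the article.** 90 centers randomized 1:1:1, so 30 per arm. "approximately six mental health providers will enroll per center, or about 540 providers total", so 180 per arm. "With a 0.025 Type I error rate, allowing for two primary comparisons between the three strategies". 80% power to detect d of "0.34–0.46 on the 8-month change of the primary outcome, assuming a between-center ICC ≤ 0.1". Direct Training change 0.14 with variance 0.0439, so SD = √0.0439 = 0.2095 and standardized change 0.14/0.2095 = 0.67.

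**Assumption.** Sidedness is not stated; two-sided is assumed. Then z(0.9875) + z(0.80) = 2.2414 + 0.8416 = 3.083.

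**Step 1. The plan's own detectable effect.** With design effect DE = 1 + (6 − 1) × ICC, d = 3.083 × √(2 × DE/180).

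| ICC | DE | d |
|---|---|---|
| 0 | 1.0 | 0.325 |
| 0.02 | 1.1 | 0.341 |
| 0.1 | 1.5 | 0.398 |

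The lower stated value, 0.34, is matched at an ICC of about 0.02. The upper value, 0.46, is not reached from the stated inputs. It appears if 25% provider loss is assumed with DE kept at 1.5: 3.083 × √(2 × 1.5/135) = 0.460. The article states 25% loss only for the client sample. Both the stated range and the no-loss value of 0.398 are therefore carried forward.

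**Step 2. Implied precision of one adjacent comparison.** SE = d/3.083; half-width of the 97.5% interval = 2.2414 × SE.

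| d at 80% power | SE (SD units) | Half-width (SD units) | Half-width on fidelity scale (× 0.2095) |
|---|---|---|---|
| 0.34 | 0.110 | 0.25 | 0.052 |
| 0.398 | 0.129 | 0.29 | 0.061 |
| 0.46 | 0.149 | 0.33 | 0.070 |

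If the observed gap were exactly zero, the interval would still include a benefit of 0.25–0.33 SD. For scale only, that is 37–50% of the 0.67 change expected within the Direct Training arm.

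**Step 3. Chance that a true step is non-significant.** Miss = 1 − [Φ(δ/SE − 2.2414) + Φ(−δ/SE − 2.2414)].

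| True step δ | d = 0.34 | d = 0.398 | d = 0.46 |
|---|---|---|---|
| 0.25 SD | 49% | 62% | 71% |
| 0.30 SD | 32% | 47% | 59% |
| 0.50 SD | 1% | 5% | 13% |

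The difficulty lies with steps below about 0.5 SD; larger steps are unlikely to be missed.

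**Step 4. Does the overall test close the gap?** Take true means 0, 0.30 and 0.60 SD. The sum of squared deviations from their mean is 0.18, and the variance of each arm mean is SE²/2. The noncentrality is 0.18/(SE²/2) = 0.36/SE², or 29.6 at SE 0.1103 and 16.2 at SE 0.1492. Against the 2-df critical value of 5.99, power is 99.9% and 96%. By simulation (correlation −0.5 between the adjacent contrasts), at least one adjacent comparison is non-significant in 59–91% of trials and both are in 4–27%. Both adjacent comparisons and the overall test all miss in only 0.1–4%. The overall test thus detects that the strategies differ somewhere, but it has no margin and does not identify which level is enough.

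**The case against.** **This is one Discussion sentence, and no passage states the harmful rule.** True. The aims, hypothesis and power statement are all about superiority, and the tests suit them. The Dissemination section speaks of identifying the most effective strategies. A reader might infer that the protocol plans to treat non-significance as proof that supervision is unnecessary. It does not say so. What stands is that the sentence claims a capability the stated tests do not have.

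**Margins and interval rules belong in the analysis plan, which is not at hand.** This is fair, and the absence of a margin is not in itself the defect. The point is that the article asserts a conclusion alongside hypotheses, error rates and power that do not lead to it. Rewording does not depend on the analysis plan.

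**A large total gap would not go unseen.** A reader might infer that the adjacent comparisons are the only tests, so that two moderate steps could both miss and leave a large Materials Only to Local Supervision gap undetected. The overall test largely prevents that (Step 4). The reason to report the outer contrast is its interval, not a lack of power to detect a difference.

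**The upper miss rates rest on a detectable effect the stated inputs do not reproduce.** Correct. With ICC 0.1 and no loss, the miss rate at 0.30 SD is 47% rather than 59%. The conclusion is unchanged.

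**Half of the Direct Training change is a tempting but weak margin.** Half of 0.67 is 0.335 SD. The 0.67 is a within-arm change from baseline, not a between-arm effect. A margin of 0.335 is 73–99% of the detectable step (0.335/0.46 to 0.335/0.34). Even with identical arms, the upper limit would fall below it only 50–79% of the time. The documents give no basis for adopting it.

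**Conclusion.** The point holds as a mismatch between a stated conclusion and the tests meant to support it. The trial can show that an added training level improves fidelity; as described, it cannot show that a lower level suffices. At the protocol's own precision, a real step of 0.30 SD would be non-significant in 32–59% of trials (47% from the stated inputs with ICC 0.1 and no loss), and a null estimate would leave 0.25–0.33 SD unexcluded.

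These figures assume two-sided testing at 0.025, normal approximations and the detectable effects in the article. The 0.30 SD step is illustrative, since the article names no smallest important difference. The superiority tests themselves are not in question, and a significant result would be fully informative about added benefit.

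**What to change.** 1. Reword the Discussion sentence to say that the trial tests whether each added level of training improves provider fidelity.
2. State that a non-significant adjacent comparison will be reported with its 97.5% interval as inconclusive, not as evidence that the lower level is enough. Apply the same rule to the brief and webinar for center directors.
3. Report the Materials Only versus Local Supervision difference and its interval from the same model.
4. If the sponsor wishes to keep the minimum-training claim, justify a between-arm fidelity margin before the 8-month outcome data are analyzed. Require the upper confidence limit for higher minus lower level to fall below it. The 0.335 SD figure should not be taken as the default.

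Items 1 to 3 cost wording and one extra contrast, with no new data. The downside is that some null comparisons will be reported as inconclusive. Item 4 may prove demanding at this sample size: with no true difference and one-sided 0.0125, the probability of meeting a margin of 0.30 SD is Φ(0.30/SE − 2.2414), which is 68% at SE 0.110 and 41% at SE 0.149.
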